#### Qualitative data

Qualitative data will be used for Specific Aim 2 (Table 1). Staff members, patients, community leaders, and government officials will be approached for KIIs and FGDs. Purposive sampling will be used, aiming to maximize heterogeneity across sex, socioeconomic position, healthcare issues, geographic location, age, caste class, and other attributes. For each group, five key informant interviews will be conducted at each time point, as described in the following. One focus group discussion per group will be conducted at each time point.

KII and FGD guides will be developed in advance, and will vary across the study period, exploring specific topics of concern. A locally validated, seven-domain framework of healthcare delivery analysis will be used to inform data collection [86]. These seven domains include health service operations, supply chains, equipment, personnel, outreach, societal factors, and structural factors. Qualitative data collection will focus on these areas to assess the implementation of the intervention.

FGDs and KIIs will occur prior to the initiation of the intervention, and at intervals of 6 months throughout the study period, to assess ongoing implementation status. All sessions will be conducted in Nepali. All qualitative data will be stored on a Research Electronic Data Capture (REDCap) database [87]. REDCap user access will be defined so that researchers only have access to de-identified study data. Any paper copies of data forms will be stored in locked cabinets inside locked rooms at district facilities. Once all data are fully transcribed and validated for quality, all paper copies will be destroyed. REDCap data will be deleted 12 months after the completion of the study period.

### Data analysis

#### Analysis for Specific Aim 1: effectiveness

In order to assess the effectiveness of the intervention, as already described, the primary outcome will utilize disease-specific “at-goal” metrics for each of the three study diseases: hypertension, type II diabetes, and COPD. We hypothesize that the integrated intervention will lead to a 10% increase in the “at-goal” status of the combined disease cohorts, over a 12-month follow-up period.

We will use conditional multivariable logistic regression to assess patient outcomes at 12 months of follow-up, adjusting for potential confounding and/or effect modification by patients’ demographics (including age, sex, caste), municipality, district, mean distance to the hospital, and engagement in care (defined as number of facility-based and community-based encounters). We additionally hypothesize a 10% improvement in the status of each of the two secondary outcomes: tobacco and alcohol use, as measured by patient-reported outcomes presented in Table 1.

As a secondary analysis for Specific Aim 1, namely the time-varying nature of the outcomes, we will assess the longitudinal effect of the intervention, as measured in 3-monthly intervals, throughout the study period, compared to baseline statistics at the time of each village-cluster enrollment. Variables will be considered either nominal or continuous (linear effect) predictors, and the generalized linear model framework will be used to estimate effect of time-varying repeated-measure intervention implementation over the several steps of the wedged design. Differential impact from time of intervention will be evaluated with test of month × intervention interaction. Models will be fit using generalized estimating equations, for example, using SAS Proc Genmod, to calculate valid standard errors in the presence of repeated measures over time and possibly correlated outcomes at the municipality level. Assumptions of overdispersion or underdispersion will be examined closely, and an estimated scale parameter or negative binomial models will be used as needed.

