### Study outcomes

The study has two specific aims: effectiveness (Specific Aim 1) and implementation (Specific Aim 2), as detailed in Table 1. For Specific Aim 1, the primary outcome will be the proportion of patients who meet disease-specific, evidence-based control measures at the completion of their initial 12 months engaged in treatment. These “at-goal” metrics aim to serve as simplified measures to assess disease control status, recognizing the limitations associated with multiple disease-specific metrics in settings like rural Nepal, especially for patients with multiple comorbid conditions. These are presented in Table 2.

**Table 1 Tab1:** Metrics for Specific Aim 1 (efficacy) and Specific Aim 2 (implementation)

Aim	Outcome/RE-AIM element	Indicator	Definition
Specific Aim 1: efficacy	Primary outcome: control of NCD conditions	Condition-specific “at-goal” metrics	% of enrolled NCD patients achieving “at-goal” status (Table 2), at completion of the study period
	Secondary outcome 1: tobacco use	Tobacco use status	% of enrolled NCD patients who were using tobacco at enrollment who are nonusers or who have reduced by > 50% their tobacco intake, at completion of the study period
	Secondary outcome 2: alcohol use	Alcohol use status	% of enrolled NCD patients who were alcohol drinkers at enrollment who are nondrinkers or who have reduced by > 50% alcohol intake, at completion of the study period
Specific Aim 2: implementation	Reach	Home visit coverage	% of enrolled NCD patients having a CHW home visit, measured monthly
		Clinic visit coverage	% of enrolled NCD patients having an MLP visit at the clinic, measured monthly according to the patients indicated to be seen that month based on protocol-based guidelines
		Demographic, geographic barriers and facilitators	% of enrolled NCD patients whose CHW has GPS-mapped their households, describing barriers/facilitators to individuals’ access, and identifying contributors to variation/inequities
		Loss to follow-up	% of patients, stratified by demographic data and NCD conditions, who are lost to follow-up after enrollment
		Monthly patient touch-points	Number of monthly per-patient touch-points, including interactions by both MLPs and CHWs
	Efficacy	Evidence-based hypertension management	% of enrolled hypertension patients in accordance with evidence-based recommendations, as prescribed by clinical algorithms, assessed quarterly by EHR audits

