### Sampling strategy and power calculations

We will use exhaustive convenience sampling to screen all eligible patients seen across two facilities over a 12-month period into the analysis cohort. Based on historical formative data of patient volume seen at these two facilities, and accounting for an expected 30% attrition rate, we conservatively expect that at least 1000 patients will be eligible for enrollment into the cohort.

With this conservative number of 1000 as our expected sample size based on this convenience sampling, we conducted power calculations to determine the statistical power to detect a change in the “at-goal” status. We calculate power based on a simplified design to compare paired proportions using a two-sided McNemar’s test with an 0.05 type I error (α) level. The primary outcome is the proportion of patients who achieve their NCD control target (“at-goal status”) after 12 months of being engaged in care. We used SAS version 9.4 (Cary, NC, USA) to estimate power to detect a 5% difference between discordant proportions; that is, proportions of patients whose “at-goal” status changed from “not at-goal” at baseline to “at-goal” at follow-up, and vice versa, in multiple scenarios where the total proportion of discordant patients ranged from 10 to 40% of all patients. Based on these assumptions, our power to detect a 5% difference in the discordant pairs is 69%, when the total discordant proportion is 40%, and the power is 99% when 10% of all patients are discordant.

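### The only model named for the 12-month primary result gives an odds ratio, which does not by itself show the size of the hypothesised rise in the at-goal proportion

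*Protocol article*

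**What the plan says.** The target is a proportion throughout the protocol article. Under Study outcomes, "the primary outcome will be the proportion of patients who meet disease-specific, evidence-based control measures", and Table 1 gives the indicator as the percentage "of enrolled NCD patients achieving “at-goal” status (Table 2), at completion of the study period". Sampling strategy and power calculations repeats it: "The primary outcome is the proportion of patients who achieve their NCD control target (“at-goal status”) after 12 months of being engaged in care".

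The hypothesis, under Analysis for Specific Aim 1: effectiveness, is that the intervention "will lead to a 10% increase in the “at-goal” status of the combined disease cohorts, over a 12-month follow-up period". The text does not say whether 10% is absolute or relative.

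Power is for a two-sided McNemar test at the 0.05 level with 1000 patients, to "estimate power to detect a 5% difference between discordant proportions", with 10 to 40% of patients discordant.

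The model for the 12-month result is given in one sentence: "We will use conditional multivariable logistic regression to assess patient outcomes at 12 months of follow-up". It adjusts for age, sex, caste, municipality, district, distance to the hospital and engagement in care. The conditioning stratum is not named, and no step takes the odds ratio back to a change in proportion. Generalized estimating equations (GEE) are named for the secondary 3-monthly analysis and for the quantitative data of Specific Aim 2, not for the 12-month primary result.

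**The concern.** Outcome, hypothesis and power calculation all concern a change in a proportion, while the named model reports an odds ratio. In a pre–post design with one baseline and one month-12 status per patient, conditioning on the patient leaves only those whose status changed. The resulting ratio says how lopsided the changes were, not how many patients changed, and the size of the rise depends on both.

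This matters for how the result will be used. The article intends it to inform policy and programme design, and Table 1 plans a cost-effectiveness analysis based on pre/post effectiveness for the primary outcomes. Both need the gain in the proportion controlled.

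The adjustment list raises a second difficulty. Most of its items do not vary within a patient, and a patient-stratified model cannot estimate main effects for them.

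**Working it through.** **Inputs.** From Sampling strategy and power calculations: N = 1000, two-sided McNemar test, α = 0.05, net difference d = 0.05, discordant proportion D = 0.10 to 0.40, stated power 69% (D = 0.40) and 99% (D = 0.10). From Analysis for Specific Aim 1: the hypothesised 10%, read here as 10 percentage points (an assumption).

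**Step 1: the plan's own power.** Normal approximation: power = Φ[(d√N − 1.96√D) / √(D − d²)].
- D = 0.40: (1.581 − 1.240)/0.630 = 0.54, giving 70.6%. The exact McNemar test gives 69.0%. Stated: 69%.
- D = 0.10: (1.581 − 0.620)/0.312 = 3.08, giving 99.9%. Stated: 99%.

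The figures reproduce, so the power calculation does rest on within-patient pairs and on d as a difference in proportions.

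**Step 2: what the conditional model estimates with patient strata.** Gainers are (D + d)/2 of all patients and losers (D − d)/2. The conditional odds ratio is their ratio, OR = (D + d)/(D − d).

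| Discordant D | OR for +5 points | OR for +10 points |
|---|---|---|
| 10% | 0.15/0.05 = 3.00 | infinite (nobody worsens) |
| 20% | 0.25/0.15 = 1.67 | 0.30/0.10 = 3.00 |
| 30% | 0.35/0.25 = 1.40 | 0.40/0.20 = 2.00 |
| 40% | 0.45/0.35 = 1.29 | 0.50/0.30 = 1.67 |

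**Step 3: the inverse.** d = D(OR − 1)/(OR + 1). For OR = 3.0, d = D/2, so the rise is 5, 10, 15 or 20 points at 10, 20, 30 or 40% discordant. For OR = 1.67 (that is, 5/3), d = D/4: 5 points at 20% and 10 points at 40%. The odds ratio does not identify d without D.

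**Step 4: check by fitting.** In 1000 simulated pairs with 254 gainers and 130 losers, a conditional logistic fit with patient strata used 254 + 130 = 384 patients, dropped the other 616 and returned OR 1.95 (254/130 = 1.95). The rise, (254 − 130)/1000 = 12.4 points, had to be computed outside the model. Over the plan's range, 100 to 400 of 1000 patients would inform such a fit.

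**Step 5: covariates.** With patient strata, a covariate enters the conditional likelihood only through its difference between month 12 and baseline. For age at entry, sex, caste, municipality, district and distance that difference is zero, so the main effect cancels. These can enter only as interactions with time, and there is then no single adjusted effect unless an averaging step is specified.

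**Step 6: precision on the proportion scale.** The 95% half-width of the paired difference is 1.96√[(D − d²)/N]. For d = 0.05 and N = 1000 it is 1.96√(0.0975/1000) = 1.9 points at D = 0.10 and 1.96√(0.3975/1000) = 3.9 points at D = 0.40.

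**The case against.** A fair opponent would make four points.

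- **The stratum is inferred.** The article does not name it, and the adjustment list sits badly with patient strata. With strata such as municipality, unchanged patients would contribute. This stands, so the statements about switching patients and covariates are conditional on patient strata. Under the other reading the output is still an odds ratio, and the within-patient pairing that the power calculation relies on would be lost.
- **The test is sound.** A reader might infer that the hypothesis cannot be checked at all. The article does not support that: without covariates, the test of OR = 1 has McNemar's null of no change in the at-goal proportion. The at-goal percentage is itself the Table 1 outcome, so a raw difference can be reported beside the model. What is missing is a named estimate of the size of the rise, in particular an adjusted one.
- **The secondary analysis need not conflict.** A reader might also infer that the GEE analysis will give a contradictory effect for the same contrast. The article describes a 3-monthly longitudinal analysis, states no link function and gives no baseline at-goal rate, so no conflict can be shown.
- **Reporting scale is often left to an analysis plan.** This is true of detail such as the form of the interval. Here, however, the article makes a definite choice of model, and that choice does not estimate the quantity in its own hypothesis.

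**Conclusion.** The point holds in a limited form. The model named for the 12-month primary result does not estimate the size of the rise that the trial hypothesises. With patient strata, odds ratios of 3.0 and 1.67 are each compatible with a gain of 5 or of 10 points inside the plan's own discordance range. Also with patient strata, the patient-constant covariates on the adjustment list have no estimable main effect.

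The conclusion rests on two readings that the article does not state: that the patient is the stratum, and that 10% is absolute. If 10% is relative, the target depends on a baseline that is not given. For assumed baselines of 20 to 50% at goal it would be 0.10 × 20 = 2 points to 0.10 × 50 = 5 points. The odds ratio would still not show whether such a target was met.

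The primary test of any change is not invalidated. The change is worth making because it lets the trial report how large the rise was, at almost no cost.

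**What to change.** In Analysis for Specific Aim 1: effectiveness:

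1. Make the primary estimate the paired difference in at-goal proportion, month 12 minus baseline, with a 95% confidence interval from all paired patients. Keep McNemar's test for the p-value, in line with the power calculation.
2. For the adjusted result, use a marginal model (binomial GEE clustered on patient), standardised to a difference in proportions.
3. Keep the conditional odds ratio as supportive, name its stratum, and say how patient-constant covariates enter.
4. State whether the hypothesised 10% is absolute or relative, and judge it from the difference in proportions.

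The cost is about one paragraph of analysis text and a few lines of code, with no new data.

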### Study populations

For primary quantitative outcomes, the study population will include adult patients (≥ 18 years of age) who qualify for a diagnosis of hypertension, type II diabetes, and/or COPD, according to WHO-PEN guidelines, and are engaged in longitudinal care by Nyaya Health Nepal’s team in Achham and Dolakha. The study will limit enrollment to the catchment areas served by both the facility-level and CHW-level services deployed by Nyaya Health Nepal. Study participants will be initially enrolled during facility-based visits at Bayalpata Hospital and Charikot Primary Health Care Center prior to the completion of intervention roll-out, and are considered engaged in longitudinal care if they have at least one follow-up hospital visit after 12 months of their initial visit. Digital health records that link between the facility-based EHR and the CHWs’ mobile-phone applications will be utilized to share patient data across settings, when available. CHWs can identify potential patients in the community and refer them to the facility for diagnosis confirmation, following which they could be included in the study. Patients’ receipt of care will not be contingent upon their enrollment in the study; all patients will continue to receive care per routine service delivery. This represents an exhaustive convenience sampling method as all eligible patients identified at Bayalpata Hospital and Charikot Primary Health Care Center may be enrolled in the study. Exclusion criteria are individuals planning to migrate from the study area prior to 12 months of exposure to the intervention, or individuals explicitly requesting exclusion from the study or declining to consent (see Additional file 3) for the study.

For implementation components, staff members, patients, community leaders, and government officials will be approached for key-informant interviews (KIIs) and focus group discussions (FGDs), as described in the following.

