## Trial status

At the time of manuscript submission, the study is currently not yet recruiting participants. Participant enrollment is anticipated to commence in February 2020 and is planned to continue for 1 year. Intervention deployment took place between July 2018 and will conclude in January 2020. This is study protocol version 1.2 and the version date is December 6, 2019.

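### The 3-monthly secondary analysis is referenced to a village-cluster start, which does not fit patient-by-patient enrolment and, on the stated dates, precedes every participant's first study reading

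*Protocol article*

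**What the plan says.** All references are to the protocol article.

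- **Analysis for Specific Aim 1: effectiveness.** The relevant paragraph opens "As a secondary analysis for Specific Aim 1, namely the time-varying nature of the outcomes". Outcomes are taken "as measured in 3-monthly intervals, throughout the study period", and the reference is "compared to baseline statistics at the time of each village-cluster enrollment". The model is meant to "estimate effect of time-varying repeated-measure intervention implementation over the several steps of the wedged design", with a test of a month-by-intervention interaction. It is fitted by GEE "to calculate valid standard errors in the presence of repeated measures over time and possibly correlated outcomes at the municipality level". No working correlation is named.
- **Study populations.** "Study participants will be initially enrolled during facility-based visits at Bayalpata Hospital and Charikot Primary Health Care Center". The same sentence places this before roll-out is complete.
- **Study design and Study outcomes.** The design is pre-post, and the outcome is taken after each patient's own first 12 months in care.
- **Sampling strategy and power calculations.** "We calculate power based on a simplified design to compare paired proportions", with 1000 patients screened in over 12 months.
- **Trial status.** "Participant enrollment is anticipated to commence in February 2020 and is planned to continue for 1 year". Intervention deployment is dated July 2018 to January 2020.
- **Table 1, Adoption rows.** Village clusters appear as places that receive or roll out the intervention. The article does not define a cluster being enrolled.

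**The concern.** The reference of a longitudinal analysis decides what its time course means. Here the unit that enters the study is the patient, but the reference is attached to a village cluster at a cluster date. The plan does not define that date, and neither plausible meaning gives a usable baseline for patients who enter one at a time over a year.

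This is the analysis meant to show how the Aim 1 effect develops. If its reference has no participants in it, the contrast cannot be formed. If the reference is a cluster's early entrants, later intervals average long-treated patients with patients who have just arrived, and the curve can look slower or weaker than what happens in any individual. A reader could then take a disagreement with the paired 12-month result as a finding, when it comes from the choice of reference.

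**Working it through.** **1. The plan's own figure.** No power is stated for this secondary analysis. The nearest figure is the paired power: N = 1000, two-sided α = 0.05, difference d = 0.05, discordant proportion p = 0.40 or 0.10.

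Normal approximation: power = Φ[(d√N − 1.96√p) / √(p − d²)].

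- p = 0.40: (1.581 − 1.240) / 0.630 = 0.54, so power is 70.6%. The exact conditional calculation gives 69.0%; the plan states 69%.
- p = 0.10: (1.581 − 0.620) / 0.312 = 3.08, so power is 99.9%. The exact calculation also gives 99.9%; the plan states 99%.

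The paired power reproduces. It belongs to the primary comparison and does not depend on the village-cluster reference.

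**2. Cluster enrolment read as roll-out.** By the Trial status section, the last cluster is reached by January 2020 and the first participant enrols in February 2020. Two consequences follow.

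- Every cluster date falls before every enrolment, so no participant has a study reading at the reference.
- Every participant's study readings fall after full deployment. The implementation indicator has the same value in all patient-intervals, so neither a step effect nor its interaction with month can be estimated.

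The Study populations section, with enrolment before roll-out is complete, cannot be true together with those dates.

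**3. Cluster enrolment read as a cluster's first entrants, with one clock for everyone.** Assumptions that are not in the document: equal entry at months 0, 3, 6 and 9; the same at-goal rate at entry in each quarter; a gain that is linear over 12 months of care and then flat; no dropout; and simple averaging over the patients present. The 10-point gain is the plan's own hypothesis.

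Apparent gain at month t = 10 × (mean months in care, each capped at 12) / 12.

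| Month on shared clock | Months in care by entry quarter | Mean | Apparent gain | Gain on own clock |
|---|---|---|---|---|
| 9 | 9, 6, 3, 0 | 4.5 | 3.75 | 7.5 |
| 12 | 12, 9, 6, 3 | 7.5 | 6.25 | 10 |
| 15 | 12, 12, 9, 6 | 9.75 | 8.1 | 10 |
| 18 | 12, 12, 12, 9 | 11.25 | 9.4 | 10 |
| 21 | 12, 12, 12, 12 | 12 | 10 | 10 |

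Continuous uniform entry over the year gives a mean of t/2 months in care up to month 12, hence 3.75 points at month 9 and 5.0 at month 12. The two clocks then agree only at month 24.

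**4. Working correlation.** The averaging in step 3 corresponds to an independence working correlation. An exchangeable one draws on within-patient change and reduces the dilution. A small simulation (60 runs per setting; 1000 patients; assumed 30% at goal at entry; assumed patient random-intercept SD of 1 to 3 on the logit scale) gave 7.8 to 9.7 points at month 12 where the true gain was 10. The plan does not say which structure applies, so the size is not fixed.

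**The case against.** **The wording may be loose.** The phrase could mean the baseline readings of the patients enrolled in each cluster, which is close to an own-patient baseline. That is possible, but the words tie the reference to a cluster's date. That the 3-monthly intervals run on a shared clock is likewise the natural reading, though not an explicit one.

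**A stepped analysis needs a cluster-start reference.** The abstract does describe stepped implementation, and in a true stepped design such a reference is natural. The defence fails on the Trial status dates, because all enrolment follows full deployment. It would regain some force only if those dates are wrong and the Study populations section is right.

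**Within-patient pairing is lost.** A reader might infer this, and with it a large loss of power. The document does not support it. GEE for repeated measures keeps within-patient correlation in the standard errors, and nothing says that enrolment readings are discarded. What goes, if the words are taken literally, is the contrast with the patient's own baseline. Power losses, or false trends from differences between early and late entrants, would depend on entry rates and a correlation structure that the document does not give.

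**The dilution is temporary.** This stands. A year of entry plus 12 months of follow-up runs to about month 24, by which time the two clocks agree if the gain persists.

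**An own baseline has its own weakness.** This also stands. Patients enter on meeting diagnostic criteria at a facility visit, so regression to the mean can inflate the change. The primary pre-post analysis already carries the same exposure.

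**Conclusion.** The reference for the 3-monthly analysis does not fit the patient-level pre-post design and should be changed. On the Trial status dates, a roll-out reference contains no participants' study readings and the stepped contrast cannot be estimated; this rests only on the stated dates. Under the first-entrants reading the time course is diluted while enrolment is open: 3.75 of 7.5 points at month 9 and 6.25 of 10 at month 12, with nothing lost by about month 21. Those sizes rest on the assumed entry pattern, linear gain and simple averaging, and would be smaller under an exchangeable working correlation.

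The scope is one secondary analysis. The primary 12-month conditional logistic regression and its paired power are untouched.

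**What to change.** In the Aim 1 analysis section:

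1. Replace the village-cluster reference with a comparison at 3, 6, 9 and 12 months since each patient's own enrolment against that patient's own enrolment reading. Enter calendar quarter of enrolment, and village cluster or municipality, as covariates.
2. Remove or redefine the terms for the steps of the wedged design and the month-by-intervention interaction. Changing the reference alone would leave the paragraph inconsistent with itself.
3. Reconcile the enrolment and roll-out timing in Study populations and Trial status, so that it is clear whether any participant is observed before roll-out in their cluster.

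The cost is a few sentences. The paired primary analysis already requires each patient's enrolment reading, so no new baseline data and no extra patients are needed. If an own-patient baseline was intended all along, the edit only says so. The remaining downside is regression to the mean, which should be acknowledged when the time course is reported.

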### Study setting

The study will take place in the Achham and Dolakha districts of Nepal across four municipalities. Following recent healthcare decentralization, Nepal’s 750 municipalities manage primary healthcare delivery. The intervention will be implemented in a step-wise fashion in coordination with municipal-level government authorities and study staff.

Achham is a remote, impoverished district of 260,000 people, with large migrant populations and a history of social disruption during the Nepali civil conflict [70–74]. Achham has one of the highest district-level under-5 mortality rates [75] and one of the lowest human development indices in the country [76]. The study implementers have been delivering some NCD-related care at the district-level Bayalpata Hospital and to communities within the hospital’s catchment population since 2008. Bayalpata Hospital serves approximately 90,000 outpatient and 3000 inpatient visits per year. CHW services include proactive case detection, care coordination, and counseling. The study will include a catchment population of approximately 50,000 in Achham across two municipalities.

The second district is Dolakha, one of the hardest hit districts in the 2015 earthquakes [77]. Nyaya Health Nepal’s work in Dolakha is based at Charikot Primary Health Care Center, which serves approximately 60,000 outpatients per year, with similar CHW services to those in Achham’s. The study will include a population of approximately 30,000 in Dolakha across two municipalities. Thus, the total expected study population will be 80,000.

Within the context of the public–private partnership between the government and Nyaya Health Nepal, no user fees are charged for any facility-based or community-based services, in either Achham or Dolakha, thereby mitigating financial access barriers to care delivery and study participation.

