#### Analysis for Specific Aim 2: RE-AIM implementation framework

In this mixed-methods study, Specific Aim 2 will be assessed using the RE-AIM framework for implementation trials [80]. A full list of metrics, separated by each domain of the RE-AIM framework, is presented in Table 1. Additional details regarding the supervision and audit structure for MLPs and CHWs can be found in Additional files 1 and 2.

For the maintenance of the intervention, we will assess the costs of the intervention, using the Joint Learning Network methodology [85]. Cost data will be analyzed and presented (Table 1) to help program planners and policy-makers understand the implications for possible scale of a similar intervention by the government or other entity in the future.

For quantitative data within Specific Aim 2, a similar methodology of generalized estimating equations, as already described in Analysis for Specific Aim 1: effectiveness, will be applied. Data will be assessed at 3-month intervals.

For qualitative data within Specific Aim 2, analysis will be ongoing and iterative, so as to continually inform further qualitative data collection, focusing on timely and relevant implementation issues. Data from KIIs and FGDs will transcribed and coded using grounded theory methodology [88, 89]. NVivo software will be used for qualitative data analysis [90].

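### With only four municipalities, the secondary GEE analyses cannot deliver the valid standard errors that the plan claims for municipality-level correlation

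*Protocol article*

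**What the plan says.** The Study setting section fixes the number of municipalities: "The study will take place in the Achham and Dolakha districts of Nepal across four municipalities". It gives two per district, with about 50,000 people in Achham and about 30,000 in Dolakha.

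The section on analysis for Specific Aim 1 names conditional multivariable logistic regression as the main analysis, with municipality and district among the adjustment variables. A further analysis follows, introduced with "As a secondary analysis for Specific Aim 1, namely the time-varying nature of the outcomes". Its purpose is to "estimate effect of time-varying repeated-measure intervention implementation over the several steps of the wedged design", using 3-monthly measurements and a test of the month by intervention interaction. These models are to be fitted by GEE, with SAS Proc Genmod as an example, "to calculate valid standard errors in the presence of repeated measures over time and possibly correlated outcomes at the municipality level".

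The Aim 2 section then applies "a similar methodology of generalized estimating equations" to its quantitative data, also at 3-month intervals. Neither section names the GEE cluster unit, the variance estimator, a small-sample correction or a reference distribution.

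**The concern.** The purpose clause is a positive statement about the method, and it depends on the number of independent clusters. For GEE to allow for correlation among patients of the same municipality, the municipality has to be the cluster. The sandwich variance then estimates between-cluster variability from four cluster totals. It is biased downwards and itself highly variable, and a normal reference distribution takes no account of either.

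If the models are run on software defaults, confidence intervals for the longitudinal effect will be too narrow, and Wald tests will find trends too often. The same goes for Aim 2 metrics modelled over time. Aim 2 matters here because the article describes the hybrid design as giving implementation and effectiveness equal priority, and the results are meant to inform programme policy.

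**Working it through.** **The plan's own figures.** The article gives no figure for how the GEE analysis performs. Its only statistical figures are for the McNemar power calculation (1000 patients, 5-point difference). Exact enumeration gives 69.0% power at 40% discordant and 99.9% at 10%, against the stated 69% and 99%, so these reproduce. They assume independent patients and do not bear on the GEE models.

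**Inputs.**
- Clusters: K = 4 (Study setting).
- Two-sided alpha: 0.05. The article states this for McNemar's test; it is assumed here for the GEE tests.
- Also assumed, because the article is silent: municipality as the cluster, an uncorrected sandwich variance, and a Wald test against 1.96.

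**Type I error, equal clusters, simple pre-post contrast.** The uncorrected sandwich variance divides by K where an unbiased estimate divides by K − 1. The robust Wald statistic is therefore sqrt(K/(K − 1)) times a t variable with K − 1 degrees of freedom, and

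type I error = P(|t with K − 1 df| > 1.96 × sqrt((K − 1)/K)).

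For K = 4 the threshold is 1.96 × sqrt(3/4) = 1.697, and P(|t3| > 1.697) = 18.8%.

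| K | Type I error |
|---|---|
| 4 | 18.8% |
| 8 | 10.9% |
| 10 | 9.6% |
| 20 | 7.1% |
| 30 | 6.4% |
| 40 | 6.0% |

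**Interval width.** The correct t3 critical value is 3.182. On the same scale the default interval uses 1.697, so its width is 1.697/3.182 = 0.53 of what is needed. Its coverage is 100% − 18.8% = 81.2%.

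**Check by simulation.** The null was simulated with 2,000 runs per scenario, 1000 patients, logistic outcomes and independence working correlation. The assumed municipality-by-time SDs were 0, 0.1 and 0.2 on the logit scale.

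| Pre-post contrast | Rejection rate |
|---|---|
| Municipality sandwich, z test, equal sizes | 18.9–19.5% |
| Same, sizes in the 50:30 district ratio | 20.5–21.1% |
| Municipality sandwich × K/(K − 1), t3 reference | 4.8–5.6% |
| Patient as cluster, municipality-by-time SD 0 | 4.7–5.7% |
| Patient as cluster, SD 0.1 | 10.8–11.3% |
| Patient as cluster, SD 0.2 | 26.5–27.7% |

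**A stepped layout.** The longitudinal model is described as stepped, but the layout of the steps is not given. Assume one municipality crossing per step, period effects and no municipality indicators. The uncorrected municipality sandwich then rejects 31–37% of the time. The K/(K − 1) correction with a t3 reference still leaves about 11–14%, so a simple correction at municipality level does not repair that model.

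**Dependence on the test.** For the same pre-post contrast, a one-degree-of-freedom empirical score statistic equals 4t²/(3 + t²). It exceeds 3.84 only when t² > 72.7, that is |t3| > 8.53, which has probability about 0.3%. That test is severely conservative, not liberal.

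**The case against.** The strongest reply is that the article fixes none of the choices behind the 19%. It gives Proc Genmod only as an example and leaves the cluster unit, variance estimator and reference distribution open. Such details commonly sit in an analysis plan, which is not shown here and may contain a small-sample correction. The planned model is also stepped, not a simple pre-post contrast, and a score test would err in the opposite direction. All of this stands. It means that 19% cannot be called the error rate of the planned analysis. It does not save the sentence itself, which claims a property that the usual robust variance lacks with four municipalities.

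A second reply is that the patient may be the intended cluster. That handles repeated measures on one person, but not correlation within a municipality over time, which the sentence says is covered.

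Stronger readings are tempting but not supported:
- *The main result is compromised.* The GEE analysis is labelled secondary, and the primary conditional logistic regression does not rest on this variance.
- *Every Aim 2 result is affected.* Many Aim 2 metrics in Table 1 are descriptive, such as percentages adopted or retained and cost breakdowns, and the article states no Aim 2 hypothesis test. Only metrics modelled over the 3-month intervals are exposed.
- *Joint tests cannot be computed.* Fitted cluster scores sum to zero, so with four clusters the robust covariance has rank at most three. Joint tests of up to three degrees of freedom remain possible. The article also allows linear time, where the interaction test has one degree of freedom. Only nominal codings needing more than three fail.

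**Conclusion.** The concern holds as a false statement about a secondary method. Neither natural reading of the text yields valid standard errors for municipality-level correlation: clustering on municipality leaves four clusters, and clustering on patients ignores the correlation at issue.

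The size is illustrative. It is about 19% instead of 5%, with intervals roughly half the needed width, under municipality clusters of equal size, a pre-post contrast, an uncorrected sandwich and a Wald z test. Under one assumed stepped layout it is 31–37%; under a score test it is about 0.3%. The point should be corrected, but it concerns the longitudinal Aim 1 analysis and the Aim 2 models over time, not the primary analysis.

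**What to change.** In the Aim 1 analysis section:

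1. Withdraw the claim of valid standard errors for municipality-level correlation.
2. Enter municipality as a fixed effect (three indicators, which also absorb district).
3. Cluster the GEE on the village cluster, which Table 1 treats as the unit of roll-out. Use a small-sample variance correction such as Mancl-DeRouen or Kauermann-Carroll, and a t reference with degrees of freedom based on the number of village clusters.
4. State that inference is to these four municipalities and that municipality-by-time variation is not covered. Fixed effects remove differences in level between municipalities, not differences in their trends.
5. Apply the same to the Aim 2 metrics that are modelled over the 3-month intervals.

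The article does not give the number of village clusters, so the precision of this approach cannot be worked out here. The plan should state the number. The table above shows why the correction is still needed: even 20 clusters would leave about 7% without it.

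The cost is a few sentences and a few lines of code. Confidence intervals will probably be wider, and the scope of inference is narrower. The article reports that recruitment had not begun, so at that point the change could be made before any outcome data.
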